#### Secondary outcome measures

Similarly, the significance of secondary endpoints on intention to stop smoking, cigarette consumption, uptake of invitation to cessation, adherence to cessation course and self-reported smoking cessation will be calculated by the χ^2^ test but the p value for the ranking scores for information on lung cancer risk and other smoking cessation aids and motivators will be estimated from the unpaired student t-test.

The open ended question: “How do you feel now about having had a genetic test that estimates the probability that you will develop lung cancer at some future date?” will have to be analysed by qualitative analysis to determine the main recurrent themes in responses.

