### Data quality assurance

The study has been designed and will be reported in accordance with CONSORT (Consolidated Statement of Reporting Trials) [25]. Data will be controlled in accordance with data protection legislation, institutional protocols of Sussex NHS Research Consortium, and NHS policies for research and information governance for ensuring patient confidentiality [26]. Data will be analysed in SPSS (Statistical Package for Social Sciences) version 15 using an intention to treat approach.

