#### Secondary endpoints

A. Personal data:

1. Number of smokers still smoking who state that they still plan to stop.

2. Daily cigarette consumption of those still smoking.

3. Mean scores for ranking of smoking cessation aids (gene-based test - Clinic A only, salivary cotinine, lung cancer facts - controls in Clinic B only and general counselling from NHS smoking counsellors).

B. Analyse questions about whether subjects would recommend the test to a member of family or a friend.

C. Analyse last (open ended) question using qualitative research methodology.

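### Daily cigarettes, a count, are assigned to a χ² test and compared only among continuing smokers, and the ranking-score t-test does not separate within-person from between-clinic comparisons

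*Protocol article*

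**What the plan says.** The Protocol article, Secondary endpoints, lists two outcomes defined on people who have not quit: "Number of smokers still smoking who state that they still plan to stop" and "Daily cigarette consumption of those still smoking". It gives no bands for consumption, no denominator for intention and no time point for either. A third endpoint is the mean score for each cessation aid, with the items split by clinic: "gene-based test - Clinic A only, salivary cotinine, lung cancer facts - controls in Clinic B only". Salivary cotinine and counselling carry no clinic limit.

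The section Secondary outcome measures then names the tests. It assigns the "secondary endpoints on intention to stop smoking, cigarette consumption, uptake of invitation to cessation", together with course adherence and self-reported quitting, to the χ² test. For the ranking scores the p value "will be estimated from the unpaired student t-test", and the text does not say which scores are set against which.

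Three other places bear on this. Data quality assurance says that data will be analysed "using an intention to treat approach". Follow-up questionnaires has each subject score several motivators and aids. The Abstract names one secondary outcome only: how the gene-based test ranks with other motivators.

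**The concern.** There are three separate mismatches between outcome and test.

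- **Scale.** A number of cigarettes per day is not categorical. χ² can be used only after the count is cut into bands. If the bands are fixed in advance, information is lost; if they are chosen after seeing the data, the result can depend on the choice.
- **Population.** Still smoking is the complement of the primary endpoint. If the gene test changes who quits, the remaining smokers in the two clinics are differently selected groups. A between-clinic p value there is no longer a randomised comparison, and it sits badly with the stated intention-to-treat principle.
- **Pairing.** Only Clinic A scores the gene test. Comparing it with cotinine or counselling, as a ranking suggests, sets two ratings by the same people against each other. An unpaired test ignores that link.

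At stake is the reading of the secondary results, including the one that the Abstract names. The primary endpoint is not affected.

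**Working it through.** The protocol gives no power or effect size for any secondary endpoint, so there is no stated figure to reproduce. The figures below are illustrations. Quit rates and group sizes come from Table 2; effect sizes, correlations and normally distributed scores are assumptions. Simulated tests are two-sided at 5% with 20,000 runs.

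**1. Who remains in the comparison.** Number still smoking = n × (1 − quit rate).

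- 6 months, 30 per group: B 30 × 0.65 = 19.5; A 30 × 0.48 = 14.4.
- 6 months, 60 per group: B 60 × 0.65 = 39; A 60 × 0.48 = 28.8.
- 8 weeks, at Table 2's 70% and 94%, 30 per group: B 30 × 0.30 = 9; A 30 × 0.06 = 1.8.

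So the subset is 65% of B and 48% of A at 6 months. At 8 weeks, if the comparison is also made then, it is 30% and 6%.

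**2. Cost of χ² on a split count.** The split is fixed midway between the two clinic means.

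| Still smoking, B v A | True difference | t-test | χ² after split | Loss (points) |
|---|---|---|---|---|
| 20 v 14 | 0 | 5.2% | 5.3% | – |
| 20 v 14 | 0.5 SD | 28.8% | 21.5% | 7 |
| 20 v 14 | 0.8 SD | 60.8% | 45.1% | 16 |
| 39 v 29 | 0 | 5.0% | 5.1% | – |
| 39 v 29 | 0.5 SD | 52.1% | 36.9% | 15 |
| 39 v 29 | 0.8 SD | 89.7% | 73.5% | 16 |

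The type I error is kept with a fixed split; the loss is in power.

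**3. Selection among continuing smokers: consumption.** Assume that the gene test has no effect on consumption and that lighter smokers quit more readily, with correlation r between baseline consumption and the tendency not to quit. At 35% v 52% quitting, the remaining Clinic A smokers are heavier at baseline by 0.08 SD (r = 0.3), 0.13 SD (r = 0.5) or 0.18 SD (r = 0.7). With an assumed SD of 7 cigarettes per day, these are 0.5, 0.9 and 1.3 cigarettes.

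Compare the standard error of the difference, SD × √(1/n_B + 1/n_A):

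- 20 v 14: √(0.0500 + 0.0714) = 0.35 SD, or 2.4 cigarettes.
- 39 v 29: √(0.0256 + 0.0345) = 0.245 SD, or 1.7 cigarettes.

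The shift is 0.08/0.35 ≈ 0.2 to 0.13/0.245 ≈ 0.5 standard errors for r up to 0.5, and at most 0.18/0.245 ≈ 0.7 at r = 0.7.

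**4. Intention to stop.** Suppose that 60% of remaining smokers in each clinic still plan to stop (assumed).

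- Counted over all randomised: B 0.60 × 65% = 39%; A 0.60 × 48% = 29%. Clinic A looks worse only because more people quit, so changing the denominator alone does not help.
- Quit or still planning: B 35% + 39% = 74%; A 52% + 29% = 81%. The composite has the right direction.

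**5. Unpaired test on ratings by the same people.** With equal variances, the squared standard error of the mean difference is 2σ²/n unpaired and 2σ²(1 − ρ)/n paired, so the ratio of standard errors is 1/√(1 − ρ). For 30 people:

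| ρ (assumed) | SE ratio | Real type I error, unpaired | Power at 0.5 SD, unpaired | Power at 0.5 SD, paired |
|---|---|---|---|---|
| 0.3 | 1.20 | 2.1% | 48% | 61% |
| 0.5 | 1.41 | 0.7% | 47% | 75% |
| 0.7 | 1.83 | 0.1% | 47% | 93% |

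**The case against.** The strongest reply concerns the t-test. A reader might infer that the unpaired test is simply wrong for the ranking scores. The protocol does not support that. It never says which scores are compared, and its list pairs the gene test in Clinic A with lung cancer facts as the control item in Clinic B. On that reading the comparison is between different people and the unpaired test fits, as it does for cotinine or counselling scored in A and in B. This stands. What remains is that the Abstract's ranking of the gene test with other motivators also implies a comparison within Clinic A, for which the named test does not fit. Even there, with positively correlated ratings, the error is conservative: it hides differences and does not create false ones.

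On selection, a reader might infer that an effective test would visibly appear to increase smoking. The figures do not show that. The shift is under one standard error in every case computed, and its inputs are assumed. The objection to the comparison rests on the loss of randomisation more than on the size of the bias. For intention, the endpoint is a number without a denominator, so the restriction is implied, not stated.

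On χ², the questionnaires identify who has cut down, a category that would suit the test, and the article refers to an additional file, not shown, for further statistical detail. Bands may be given there. But the endpoint as listed is daily consumption, not cutting down, so the stated test and the stated outcome still disagree.

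Finally, the remedy has limits. With quitters at zero, consumption partly repeats the primary endpoint, and the composite may sit near its ceiling in volunteers who already want to quit.

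**Conclusion.** The point holds in a limited form, for secondary endpoints only.

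- **χ² for cigarettes per day:** it does not fit the endpoint as defined. The cost is roughly 7 to 16 points of power for assumed differences of 0.5 to 0.8 SD, with type I error intact if the bands are fixed in advance.
- **Continuing smokers only:** a between-clinic test would use a post-randomisation subset, about 65% of B and 48% of A at 6 months on the protocol's own rates. The bias in consumption is probably small, about 0.1 to 0.2 SD if lighter smokers quit more readily, but it runs against an effective test.
- **Ranking scores:** the comparison is not defined. The unpaired t-test is valid between clinics and unsuitable within Clinic A, where its real type I error is about 0.7% at an assumed correlation of 0.5 and power for a 0.5 SD difference falls from 75% to 47% in 30 people.

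This is worth correcting because the repair is cheap. It does not put the trial's main conclusion at risk.

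**What to change.** Amend the wording of Secondary outcome measures and Secondary endpoints:

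1. Compare cigarettes per day between clinics in all randomised subjects, with quitters set to 0, by a Wilcoxon rank-sum test. State how subjects without a consumption report are ranked, since the protocol expects 40–50% drop-out.
2. Compare the proportion with verified quit or still planning to quit over all randomised subjects; χ² suits this.
3. Report consumption and intention among continuing smokers by clinic as description, without a p value.
4. List the ranking comparisons. Keep the unpaired t-test for Clinic A versus Clinic B. Use a paired t-test or Wilcoxon signed-rank test for the gene test against each other aid scored by the same Clinic A subjects.

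Optionally, score the fact sheet in both clinics, since both receive it; this adds one item to the Clinic A questionnaire and would allow a within-person comparison with the gene test.

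The cost is analysis text only, with no change to recruitment, treatment or sample size. The price is interpretive: the all-randomised consumption result should be presented as overlapping with the primary endpoint, and a high composite rate in both clinics would leave little room to show a difference.

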## Discussion

### Overview

Smoking cessation is one of the most cost effective interventions that can be achieved in primary care [29]. However many smokers are very reluctant to commit to a smoking cessation programme (precontemplative and contemplative) and about half of those that attend for smoking cessation intervention (action stage of change) are likely to drop out or give up trying. Therefore, any methodology that increases motivation in both unmotivated and motivated smokers could be very valuable. The gene-based test we are offering has shown promise as a smoking cessation motivator in precontemplative-contemplative smokers in a hospital outpatient setting [15,18] and now needs to be tested out as a motivator for improving adherence in a primary care smoking cessation clinic using a randomised controlled study.

### Strengths

The main strengths of this study are that it is being carried out on subjects from a large primary care population and should therefore be more representative of the general population than previous studies recruited from hospital patients and other special groups. We also have the advantage of being able to carry out this research within the established framework of the local stop smoking service.

### Limitations and assumptions

Although we have estimated, based on previous smoking cessation work using this gene-based test, that the primary endpoint will show that having the test improves quit rate by 20-25%, this was based on a cohort of hospital outpatients in Auckland, New Zealand and subjects recruited from primary care may respond differently. Although we plan to recruit a minimum of 60 subjects, this may not be enough to balance unexpected and unknown confounding factors.

### What we might find

We aim to recruit a minimum of 60 subjects to randomise 30 into group A (test group) and 30 into Group B (control group). The normal experience in NHS smoking cessation clinics is a drop-out rate of 40-50% [30-32]. We need, therefore, to attempt to recruit about 120 subjects in order to get a statistically significant result, based on the assumptions in our power calculations. We may, however, have underestimated the 6-month quit rate using the NHS local stop smoking guidelines [22] which typically involves a multi-interventional programme which includes combinations of varenicline prescriptions, breath carbon monoxide monitoring and intensive counselling giving a quit rate of 70-80% at 6-weeks.There are however no Surrey data for 6-month quit rate which we assume, on the basis of similar smoking cessation data to be about half the 6-week figure [33] ≅ 35%.

An unknown and unpredictable factor, that could skew results significantly, is the possibility that our multi-interventional approach could help to reinforce the health risk message equally for subjects in both groups. Also, the Auckland study design involved recruitment of precontemplative-contemplative smokers from a hospital outpatient setting, compared to this study that will involve primary care subjects who have volunteered to participate in a smoking cessation programme (ie smokers in the action stage of quitting). This population, therefore, could be sufficiently different to give unexpected results. However, the results of this trial will inform as to the acceptability of this approach as well as its effectiveness.

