### 2/ Recruitment

Subjects will be recruited from a large general practice in Surrey (practice population= > 30,000). Smokers aged 20-70 years will be identified from the practice records and contacted by post by their GP. Patients who reply stating that they wish to stop smoking will be randomised (stratified randomisation to ensure equivalent age and gender mix) to two clinics (Figure 3) only one of which will include the gene-based test. Previous trials of genetic testing in association with smoking cessation achieved 83-100% of participants opting for the test depending on the method of recruitment [8,21]. There will be two mailings with SAEs for recruitment with the aim of recruiting at least 30 subjects per clinic (see Power calculations under heading “statistics”). In the first letter the patient’s GP asks the patient to give permission for the researcher to contact him/her to ask about taking part in smoking cessation research (with possible genetic risk testing) and encloses fact sheet 1 and a stamped addressed envelope (SAE) for reply.

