### Statistics

#### Primary end point

The difference between smoking cessation between Clinic A and Clinic B will be estimated from the four week and six month follow up for the primary endpoint (smoking status confirmed by carbon monoxide breathalyser and salivary cotinine tests). If there is the expected higher rate of smoking cessation for Clinic A compared with Clinic B, statistical significance will be demonstrated by the χ^2^ test.

Since there are, as yet, no case-control studies that compare quit rate following the gene-based test versus quit rate without the test, the expected difference in quit rate between Clinic A and Clinic B is difficult to estimate. Two case-control studies showing only a 5-10% increase in smoking cessation involved just a single gene of small effect [11,12]. In a randomised control trial patients were given either a full explanation of the results of spirometry testing, including an estimation of lung age or just the FEV1, without explanation (control group). The group of patients who were given the full explanation had a 7.2% higher quit rate than the control group. However, data from Auckland suggest a larger uplift of quit rate with *Respiragene.* This can be explained by the superior predictive power of a 20-gene test combined with clinical history (personal history of COPD and family history of lung cancer) to give a rather more impressive estimate of cancer risk than anything previously available.

The adequacy of sample size was tested using data from smoking cessation trials that showed:

•30-40% smoking cessation at 6-months with similar protocols [27,28].

•A 48% quit rate at 2-4 weeks in subjects with high and very high lung cancer risk scores but this difference shrinks to 27% at 6 months.

•Data from Young et al [15,18] (independently verified by McBride et al [11]) that even being given an average score for lung cancer susceptibility increases smoking cessation by approximately 10%.

Therefore, with a minimum sample sizes of 30 per group the following calculations based on these estimated quit rates apply (Table 2). Statistical power of 87.1% is generally acceptable for publication (for alpha error of 5% - i.e. 5% probability of incorrectly rejecting the null hypothesis that there is no difference in the percentage values). For further detailed statistical analysis, refer to Additional file 1.

**Table 2 T2:** Summary of values from which the power of the study are estimated

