		**Control group expected quit rate as %ge**	** *Respiragene * ****group expected quit rate as %ge**	**χ**^**2 **^**calculated from four-some table**	**P value based on χ**^**2**^	**Power calculations***
8 weeks	Sample size 30/30*	70%	94%	5.9	<0.05	79.3%
	Sample size 60/60*			11.7	<0.01	96.9%
6 months	Sample size 30/30**	35%	52%	1.7	NS	36.5%
	Sample size 60/60**			6.2	<0.05	87.1%

*Telephone (alone) quit rate (see Table 1) assumed to be 20%.

**Telephone (alone) quit rate (see Table 1) assumed to be 10-15%.

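### About 120 recruits, less the stated 40-50% drop-out, leave 30-36 per arm: enough for the 8-week row of Table 2 but not for a significant six-month result

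*Protocol article*

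**What the plan says.** In the protocol article, *What we might find* sets a minimum of 60 subjects, "to randomise 30 into group A (test group) and 30 into Group B (control group"). It then reports that "The normal experience in NHS smoking cessation clinics is a drop-out rate of 40-50" per cent, and concludes that it is necessary "to attempt to recruit about 120 subjects in order to get a statistically significant result", on the assumptions of the power calculations. *2/ Recruitment* states the same floor, "with the aim of recruiting at least 30 subjects per clinic".

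Table 2 has two rows for each timepoint:

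- 8 weeks, 70% vs 94%: at 30/30, chi-squared 5.9, p<0.05, power 79.3%; at 60/60, chi-squared 11.7, p<0.01, power 96.9%.
- Six months, 35% vs 52%: at "Sample size 30/30", chi-squared 1.7, NS, power 36.5%; at 60/60, chi-squared 6.2, p<0.05, power 87.1%.

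The text above the table (*Statistics, Primary end point*) names a minimum of 30 per group and then describes 87.1% as an acceptable power, "for alpha error of 5" per cent. It adds that "statistical significance will be demonstrated by the χ^2^ test". Under *Outcome measures*, the primary endpoint covers both 8 weeks and six months, and the *Hypothesis* is about six months. *Data quality assurance* says the data will be analysed "using an intention to treat approach".

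**The concern.** The figure of 120 is what results from inflating 30 per arm for 50% drop-out. It is therefore sized to leave the 30/30 rows of Table 2, not the 60/60 rows. At six months the 30/30 row is the one the authors label NS. The only power the text calls acceptable, 87.1%, belongs to six months at 60/60. The sentence that justifies the target thus claims something that the table it relies on does not show for six months.

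A reader would take 120 recruits as enough to answer the six-month question. With a one-in-four to one-in-three chance of detecting the planned effect, a non-significant result would be likely even if the effect were real, and could be misread as evidence that the test does not help.

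**Working it through.** **Inputs.** Recruitment 120, taken as 60 per arm because the minimum is split 30:30; drop-out 40-50% (*What we might find*). Rates 70% vs 94% at 8 weeks and 35% vs 52% at six months (Table 2). Alpha 5%, sidedness not stated; chi-squared test (*Statistics, Primary end point*).

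**Step 1: where 120 comes from.** 30/(1 − 0.5) = 60 per arm, or 120 in total. In reverse, 60 × 0.5 = 30 and 60 × 0.6 = 36 completers per arm.

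**Step 2: reproduce Table 2.** With p̄ the mean of the two rates and d their difference:

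- chi-squared = d² / (2p̄(1 − p̄)/n)
- power = Φ{[d − z√(2p̄(1 − p̄)/n)] / √[(p₁(1 − p₁) + p₂(1 − p₂))/n]}, with z = 1.96 two-sided or 1.645 one-sided

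| Row | Chi-squared: stated / recomputed | Power: stated | One-sided | Two-sided |
|---|---|---|---|---|
| 8 weeks, 30/30 | 5.9 / 5.85 | 79.3% | 79.3% | 68.6% |
| 8 weeks, 60/60 | 11.7 / 11.71 | 96.9% | 96.9% | 93.8% |
| 6 months, 30/30 | 1.7 / 1.76 | 36.5% | 37.4% | 26.1% |
| 6 months, 60/60 | 6.2 / 3.53 | 87.1% | 59.4% | 46.7% |

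Three of the four rows match a one-sided 5% calculation, exactly or within a point. The six-month 60/60 row does not match. There p̄ = 0.435 and d = 0.17, so chi-squared = 0.0289/(0.49155/60) = 3.53, below the 3.84 needed for p<0.05. The printed 87.1% equals the one-sided power for 35% vs 60% at 60 per arm, not 35% vs 52%. The chi-squared test as planned is two-sided, so the two-sided column is the relevant one.

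**Step 3: what 120 delivers among completers.**

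- Six months, n = 30: (0.17 − 1.96 × 0.1280)/0.1261 = −0.64, power 26.1% two-sided (37.4% one-sided).
- Six months, n = 36: chi-squared 2.12, power 30.4% two-sided (42.4% one-sided). Table 2 has no row for this size; it is a recomputation.
- Six-month 95% CI half-width: 1.96 × √(0.4771/n) = 24.7 points at n = 30 and 22.6 at n = 36.
- 8 weeks, n = 30 to 36: power 68.6-76.6% two-sided (79.3-85.5% one-sided).

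**Step 4: what 120 delivers if all are kept under intention to treat.**

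- If 35% and 52% apply to everyone randomised, this is the corrected 60/60 row: 46.7% two-sided, 59.4% one-sided.
- If 35% and 52% are instead rates among completers and drop-outs count as smoking, the rates shrink by a factor of 0.6 or 0.5. 21% vs 31.2% gives 24.4% two-sided power, and 17.5% vs 26% gives 20.2%. The same assumption at 8 weeks gives 42% vs 56.4% (35.0%) or 35% vs 47% (26.5%).

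**Step 5: scale.** Keeping 60 completers per arm would take 60/0.6 = 100 to 60/0.5 = 120 recruits per arm, or 200-240 in total.

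**The case against.** The sentence in *What we might find* names no timepoint. Eight weeks is also primary, and Table 2 shows 30/30 at 8 weeks as significant with 79.3% power, so for that row the inflation to 120 is done correctly. This stands and limits the point to six months. It does not remove the point, because six months is equally primary and is the timepoint of the hypothesis, and the 87.1% cited in the text is a six-month figure.

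A second defence is that under intention to treat all 120 remain, so the 60/60 row applies. It fails on arithmetic, since that row does not follow from its own rates.

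A reader might go further and infer that 40-50% drop-out makes 70% and 94% at 8 weeks impossible, because no arm could then exceed 50-60% verified quitters. The document does not support that as a flat statement. It needs the loss to fall by week 8, whereas *4/Smoking cessation clinics* expects good attendance over the eight weeks and sees the difficulty at six months. It needs the same loss in both arms, whereas the drop-out figure describes usual NHS clinics and better adherence is part of the research question. It also needs drop-outs to count as smokers, a rule the article does not state and may properly leave to the analysis plan. Biochemical confirmation of status makes that rule plausible but does not establish it.

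Nor is 120 a stopping rule: the wording is an attempt to reach about that number, with a minimum of 30 per clinic. The authors also print the NS and the 36.5% openly and warn of unexpected results.

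**Conclusion.** The point holds for six months. On the document's own figures, the 120 target leads to the row that Table 2 labels NS with 36.5% power. Recomputed with the two-sided test, power is 26-30%. No reading of the 120 brings it to the stated 87.1%: the most favourable, 60 per arm with undiluted rates, gives 47% two-sided or 59% one-sided.

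The core contradiction needs only the stated drop-out, equal allocation and Table 2. The two-sided figures assume the usual chi-squared test at 5%. The 20-24% figures rest on two further assumptions, that the planning rates are completer rates and that drop-outs count as smoking, and should be read as a sensitivity case. The 8-week planning rates of 70% and 94% are unattainable only if the 40-50% loss falls by week 8 in both arms and drop-outs are counted as smokers.

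**What to change.** - In *What we might find*, delete the claim that about 120 recruits give a statistically significant result as far as six months is concerned. Say instead that 120 recruits are expected to leave 30-36 completers per arm, with about 26-30% two-sided power at six months for 35% vs 52% and a 95% CI half-width of about 23-25 points. The 8-week comparison can keep its support, stated as 69-77% two-sided.
- In Table 2, correct the six-month 60/60 row to chi-squared about 3.5, NS, power about 47% two-sided (59% one-sided). Say whether the powers are one- or two-sided.
- In *Statistics, Primary end point*, remove or replace the 87.1%.
- State power on the same denominator as the planned intention-to-treat analysis. Give the diluted-rate figures (about 20-24% at six months, 27-35% at 8 weeks) as a sensitivity case, with the assumption spelled out that unverified participants count as smoking and that the planning rates are completer rates.

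The cost is a few sentences and table entries, and a stated power that is less favourable. No added recruitment is involved.
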